**Methods:**

PSWs will lead a typical informal peer support group within the larger context of online peer support groups, focusing on personal-civic recovery. They will be scripted with a fixed, predetermined duration (a series of 10 weekly 90-minute online workshops). There will be 2 experimental subgroups—patients diagnosed with (1) psychotic disorders (n=10) and (2) anxiety or mood disorders (n=10)—compared to a control group (n=10). Random assignment to the intervention and control arms will be conducted using a 2:1 ratio. Several instruments will be used to assess clinical recovery (eg, the Recovery Assessment Scale, the Citizenship Measure questionnaire). The COVID-19 Stress Scales will be used to assess effects in terms of clinical recovery and stress- or anxiety-related responses to COVID-19. Changes will be compared between groups from baseline to endpoint in the intervention and control groups using the Student paired sample t test.

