#### Planned Trial Interventions

##### Control Intervention

When a person shows up at the Emergency Department of IUSMM for the first time, he or she is systematically approached by a research nurse after a first medical authorization is granted for that person to be approached (sometimes this authorization is not granted for medical or security reasons). The research nurse then explains the objectives of the Signature Bank project and invites the person to participate. Those who agree to participate sign the Information and Consent Form (T1), fill out a series of questionnaires, including ones on sociodemographics; consent to the taking of biological samples; and asked if they are willing to be contacted for other research purposes (like our own study). Then, as with any other IUSMM patients, they are evaluated by the Evaluation and Liaison Module during their hospital stay. A diagnostic is established or confirmed by ward psychiatrists and coded according to the WHO International Classification of Disease–10th Revision (ICD-10) [79]. Based on the diagnosis (or diagnoses), after discharge (T2), they are referred to a specialized outpatient clinic (T3). Whether for psychotic disorders or for anxiety and mood disorders, pharmacotherapy, psychotherapy, or a combination of both are then offered in accordance with the guidelines of the Royal College of Physicians and Surgeons of Canada. Of the Signature Bank participants diagnosed with psychotic disorders, or anxiety or mood disorders, and who consent to participate in our study, half will receive only the control intervention, while the other half will also receive our experimental PSW-led online group intervention (random allocation control/experimental intervention ratio=2:1).

Inclusion criteria include patients recruited from the Signature Bank data collection project diagnosed with (1) schizophrenia and psychotic disorders (ICD F20-F29), or with (2) anxiety or mood disorders (ICD F30-F49), (3) aged 18 years old or more, and (4) who have already consented to be contacted by telephone to be invited by our team to participate in this pilot study. Exclusion criteria include (1) active suicidal intentions, (2) marked cognitive impairment, and (3) no access to an electronic device with a webcam and microphone to participate in the online transitional peer support group.

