#### Allocation

Upon reception of the signed Information and Consent forms by email, consecutive referrals will be randomly allocated by computer algorithm to one of the two modalities at point of entry into the study on acceptation into the protocol using a computerized program (eg, randomization.com). At this entry point, the participant will have been evaluated, diagnosed, met inclusion criteria, and given formal consent for the randomization procedure. To ensure a balance in the allocation for the strata and thus control the risk of a secular trend in the composition of groups, random block sizes in a random order will be used (3, 6, 9, etc). Participants will thus be randomly allocated to the trial arm (n=20, 2 groups of 10) or control arm (n=10), and will be identified by a randomly assigned identification number. Among those allocated to the experimental groups, 10 patients with psychotic disorders will be randomly selected to be part of the transitional support group for patients with psychotic disorders, and 10 patients with anxiety or mood disorders will be randomly selected to be part of the transitional self-help group for patients with anxiety or mood disorders. It will be the same for the control group; 5 patients with psychotic disorders will be randomly selected to be part of the control group for patients with psychotic disorders, and 5 patients with anxiety or mood disorders will be randomly selected to be part of the control group for patients with anxiety or mood disorders. In both cases, those who have not been selected will be placed on a substitute list in the event of withdrawal of a selected patient, who will be replaced at random by one of the corresponding substitutes.

The groups will be studied together and separately: the experimental group for patients with psychotic disorders (n=10) will be compared to the control group for patients with psychotic disorders (n=5); the experimental group for patients with anxiety or mood disorders (n=10) will be compared to the control group for patients with anxiety or mood disorders (n=5); and the combined experimental group for patients with psychotic disorders and for patients with anxiety or mood disorders (n=20; 2×10) will be compared to the combined control group for patients with psychotic disorders and anxiety or mood disorders (n=10).

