#### Quantitative Analyzes

Baseline characteristics will be summarized, including for the measures of clinical recovery (see the *Outcome Measures at Follow-up* section), the Recovery Assessment Scale, the Citizenship Measure (personal-civic recovery), the COVID-19 Stress Scales, and the Bem Sex Role Inventory. All participants with data at baseline (T1) and follow-up will be included in the analyses. We will compare within-patient change from baseline to intervention versus control group in the study outcome measures using the Student paired sample *t* test. The analysis will run on intervention and control practices separately so as to explore practice level impact on the differences in outcomes. Comparison of confidence interval and effect size between groups will be assessed.

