**Total eligible participants (N=92)**		
	Participants with AMD^a^	31 (33.7)
	Participants with PD^b^	61 (66.3)
**Total eligible participants who agreed to receive the ICF^c^ by email (N=92)**		54 (58.7)
	Participants with AMD (n=31)	23 (74.2)
	Participants with PD (n=61)	31 (50.8)
**Total eligible participants who returned the signed ICF (n=54)**		36 (66.7)
	Participants with AMD (n=23)	17 (73.9)
	Participants with PD (n=31)	19 (61.3)
**Total eligible participants who completed the questionnaires at T1 (n=36)**		32 (88.8)
	Participants with AMD (n=17)	16 (94.1)
	Participants with PD (n=19)	19 (100.0)
**Total eligible participants who completed the questionnaires at T2 (n=30)**		24 (80.0)
	Participants with AMD in the experimental group (n=10)	7 (70.0)
	Participants with PD in the experimental group (n=10)	10 (100.0)
	Participants with AMD or PD in the control group (n=10)	7 (70.0)

^a^AMD: anxiety and mood disorders

^b^PD: psychotic disorders.

^c^ICF: Information and Consent Form.

**Table 2 table2:** Calendar of activities.

Date	Activity	
	Convergent and Concurrent Validity Between Clinical Recovery and Personal-Civic Recovery	Effects of Online and Recovery-Oriented Peer Support Groups Facilitated by Peer Support Workers
	ClinicalTrials.gov ID NCT04125030	ClinicalTrials.gov ID NCT04445324
September 2019 to March 2020	Study suspended due to the COVID-19 pandemic 92 eligible participants completed the study	—^a^
April-May 2020	—	Writing and submission of the research protocol to the institutional review board
June 2020	—	Institutional review board approval of research protocol
July 2020	Submission of the study protocol for publication in a peer-reviewed journal	Submission of the study protocol for publication in a peer-reviewed journal
August 2020	—	Recruitment of study participants among those 92 from the previous validation study Precompletion of measures (T1)
September to October 2020	Publication of the research protocol [100]	10 weekly peer support groups for patients with psychotic disorders 10 weekly peer support groups for patients with anxiety or mood disorders
November 2020	Data analyses	Postcompletion of measures (T2) Addenda to study protocol Submission of the revised study protocol for publication
December 2020	Submission of the study’s main conclusions for publication in an open access peer-reviewed journal	Data analyses Submission of the study’s main conclusions for publication in an open access peer-reviewed journal

^a^Not applicable.

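### Allocation is fixed within diagnosis, but the combined 20 v 10 comparison has no diagnosis term: if change differs by diagnosis it is conservative as planned and could be confounded among Table 1 completers

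*Protocol article*

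**What the plan says.** The Allocation section of the protocol article uses random blocks, with the aim "To ensure a balance in the allocation for the strata". It sets the arms at 20 and 10 and fills them by diagnosis: 10 psychotic and 10 anxiety or mood in the experimental arm, 5 and 5 in the control arm. Three comparisons follow: 10 v 5 in psychotic disorders, 10 v 5 in anxiety or mood disorders, and a combined one in which the 20 experimental participants "will be compared to the combined control group for patients with psychotic disorders and anxiety or mood disorders (n=10").

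On method, the Quantitative Analyzes section says: "We will compare within-patient change from baseline to intervention versus control group in the study outcome measures". The test named there and in the abstract is the Student paired t test. It is run in each arm separately, after which confidence intervals and effect sizes are compared between groups. Only participants with both baseline and follow-up data are analysed. The only stratified analysis named is by sex (Sex and Gender section).

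Table 1 gives the follow-up completers: 10 of 10 psychotic and 7 of 10 anxiety or mood in the experimental arm. The controls stand in one undivided row, "Participants with AMD or PD in the control group (n=10"), with 7 completers.

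**The concern.** Diagnosis is fixed by design and used in two of the three comparisons, but no term for it is named in the third. If the two diagnoses change by different amounts, two things follow. At the planned counts, the between-diagnosis variation stays in the error term although the design has already removed it from the arm difference, so precision is given away in a study of 30. And if completion differs by diagnosis and arm, the unadjusted pooled difference can mix the effect of the intervention with the diagnosis mix. Table 1 already shows unequal completion by diagnosis in the experimental arm.

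**Working it through.** **Inputs from the article.** Planned cells 10/10 experimental and 5/5 control (Allocation). Completers 10 psychotic and 7 anxiety or mood in the experimental arm, and 7 controls of unstated diagnosis (Table 1). The counts agree: 10 + 10 = 20, 5 + 5 = 10, 10 + 7 + 7 = 24, and 24/30 = 80.0% as printed. The article states no power, alpha or effect size, so there is no such figure to reproduce. The Control Intervention section describes the ratio differently ("random allocation control/experimental intervention ratio=2:1", and halves). I use the 20 v 10 of the Allocation section, which agrees with the abstract.

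**Assumptions, not in the article.** Within-diagnosis SD of change is 1. The difference in mean change, psychotic minus anxiety or mood, is d = 0.5 to 1.0 SD. Two-sided alpha is 0.05. The comparison is between arms, on change. Reversing the sign of d reverses every bias below.

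**Step 1: planned counts.** Both arms are 50% psychotic, so the pooled difference has no bias from diagnosis. Its true standard error is sqrt(1/20 + 1/10) = 0.387 SD. The unadjusted analysis estimates the variance as (28 + 30 × d²/4)/28, so its standard error is too wide by the square root of that:

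- d = 0.5: sqrt(29.875/28) = 1.03
- d = 0.8: sqrt(32.8/28) = 1.08
- d = 1.0: sqrt(35.5/28) = 1.13

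In two sets of simulations, type I error of the unadjusted test was 4.3% to 4.5% at d = 0.5, 3.4% to 3.5% at d = 0.8 and 2.8% at d = 1.0. With diagnosis in the model it was 5.0% at every d. Power for an assumed effect of 0.8 SD (normal approximation) is 54.2% adjusted. Unadjusted, it is 51.8% at d = 0.5 and 45.5% at d = 1.0.

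**Step 2: Table 1 completers.** The experimental arm is 10/17 = 58.8% psychotic. If the 10 controls were 5 and 5 as planned, the 7 completers include k = 2 to 5 with psychotic disorders. Bias = d × (10/17 - k/7).

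| Controls, psychotic / anxiety or mood | Imbalance (points) | Bias, d = 0.5 | Bias, d = 0.8 | Bias, d = 1.0 |
|---|---|---|---|---|
| 2 / 5 | +30.3 | +0.15 | +0.24 | +0.30 |
| 3 / 4 | +16.0 | +0.08 | +0.13 | +0.16 |
| 4 / 3 | +1.7 | +0.01 | +0.01 | +0.02 |
| 5 / 2 | -12.6 | -0.06 | -0.10 | -0.13 |

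Type I error of the unadjusted test exceeds 5% only in the first row: 5.5% at d = 0.5 and 6.3% at d = 1.0. In the other rows the excess width of the standard error outweighs the bias. With a diagnosis term the bias is zero in every row, type I error is about 5%, and the standard error is 0.449 to 0.467 SD.

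**The case against.** **The article is condensed, and covariates are often left to an analysis plan.** That is true, and an unseen plan may add the term. But the article itself chooses both the combined comparison and the test, and the named test cannot carry a diagnosis term. The text as it stands needs the change.

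**The figures are for a between-arm comparison, not for the paired test named.** This stands as a limit on the numbers. That a paired test within each arm does not itself test the arm difference is a separate fault. The widening is nearly the same inside an arm, though. For n participants split evenly it is sqrt((n - 1 + n × d²/4)/(n - 1)). At d = 1.0 that gives sqrt(24/19) = 1.12 for n = 20 and sqrt(11.5/9) = 1.13 for n = 10.

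**Level is not change.** The outcome is within-patient change, so stable differences in level between diagnoses cancel. It would be wrong to argue from the fact that the PSQ, PHQ-9 and STAI-Y6 target different disorders. Those are secondary outcomes, and the primary one, personal-civic recovery, is not specific to a diagnosis. Only a difference in mean change matters, and the article gives none. This stands, and it makes every size above conditional.

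**Two stronger readings are not supported.** A reader might infer that the intervals of the combined comparison are simply wrong. At the planned counts they are correct if d = 0 and otherwise too wide, never too narrow. A reader might also infer from Table 1 that the diagnostic balance has been lost and the pooled result is confounded. The control row is not split, and a 4/3 split would leave an imbalance of 1.7 points. Nor does the plan ignore diagnosis altogether, since it makes a comparison within each one.

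**Conclusion.** The point holds in a limited form. The combined comparison, as described, has no term for the factor on which allocation was fixed. At the planned counts the cost is precision, not validity: for a difference in change of 0.5 to 1.0 SD, a standard error about 3% to 13% too wide and a type I error of about 4.4% to 2.8%. At the lower end this is small for a feasibility study. Among the Table 1 completers, confounding by diagnosis is possible but not shown. At an assumed 0.8 SD the bias lies between -0.10 and +0.24 SD, depending on a control split that the article does not report.

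All of this rests on an assumed difference in mean change, equal variances and 5 + 5 controls at allocation. That adjustment removes the bias also assumes a similar intervention effect in both diagnoses and no other selective dropout within a diagnosis. The change is worth making because it costs almost nothing and matches the design.

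**What to change.** In the Allocation and Quantitative Analyzes sections, define the combined comparison as a between-arm linear model of change (or of follow-up adjusted for baseline) on arm plus diagnosis. Report the arm effect with its 95% confidence interval. The diagnosis term costs one degree of freedom and needs no new data, since diagnosis is an entry criterion.

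Report the two diagnosis-specific estimates, with confidence intervals, from a separate model that adds arm x diagnosis. That model uses two degrees of freedom more than the unadjusted one. Keeping it separate means the combined arm effect does not depend on how unequal cells are weighted.

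When results are reported, splitting the control completers by diagnosis would let readers see which row of the table above applies.

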#### Protecting Against Sources of Bias

IUSMM clinical staff will receive no information on how participants scored on the Recovery Assessment Scale and Citizenship Measure questionnaires. PSWs will receive no information on participants’ results related to clinical recovery measures routinely taken for the Signature Bank. The PSWs will be separated from the outpatient clinic therapists and will sign agreements not to discuss cases.

#### Primary and Secondary Outcome Measures

Several instruments have been developed by clinicians and academics to assess clinical recovery. Based on their life narratives and to assess personal-civic recovery, measurement tools have also been developed through community-based participatory research and validated by persons living with MHPIs (eg, the Recovery Assessment Scale and the Citizenship Measure questionnaires). As users of mental health services typically tend to prefer interventions to help them recover, reintegrate with society, and achieve their personal goals [92], we propose this pre-post research feasibility trial design to evaluate the outcomes on personal-civic recovery (primary outcome), on clinical recovery and stress- or anxiety-related responses to the COVID-19 pandemic (secondary outcome).

#### Outcome Measures at Follow-up

The COVID-19 Stress Scales (36 items) and the measures of personal-civic recovery (47 items) will be repeated, along with the following measures of clinical recovery, which are routinely collected among all Signature Bank participants:

Anxiety: Anxiety State-Trait Anxiety Inventory Form Y6, 6 items (STAI-Y6) [93];Depression: Depression Patient Health Questionnaire, 9 items (PHQ-9) [94];Alcohol dependence: Alcohol Use Disorders Identification Test, 10 items (AUDIT-10) [95];Drug dependence: Drug Abuse Screening Test, 10 items (DAST-10) [96];Psychosis: Psychosis Screening Questionnaire, 12 items (PSQ) [97]; andSocial functioning: WHO Disability Assessment Schedule, 12 items (WHODAS 2.0) [98].

##### The COVID-19 Stress Scales

Research and clinical observations suggest that during times of pandemic many people exhibit stress- or anxiety-related responses that include fear of becoming infected, fear of coming into contact with possibly contaminated objects or surfaces, fear of foreigners who might be carrying infection (ie, disease-related xenophobia), fear of the socioeconomic consequences of the pandemic, compulsive checking of and reassurance seeking related to possible pandemic-related threats, and traumatic stress symptoms about the pandemic (eg, nightmares, intrusive thoughts). Taylor et al developed the 36-item COVID-19 Stress Scales to measure these features, as they pertain to COVID-19. The COVID-19 Stress Scales were developed to better understand and assess COVID-19–related distress. A stable 5-factor solution was identified, corresponding to scales assessing COVID-19–related stress and anxiety symptoms: (1) concerns related to danger and contamination (12 items, Cronbach α=0.94); (2) concerns about economic consequences (6 items, Cronbach α=0.90); (3) xenophobia (6 items, Cronbach α=0.92); (4) traumatic stress symptoms (6 items, Cronbach α=0.93), and (5) compulsive checking and reassurance seeking (6 items, Cronbach α=0.83). In collaboration with the original authors (ie, [name]), we have translated the COVID-19 Stress Scales into French, and it can be completed using a 5-point Likert scale.

##### The Recovery Assessment Scale

Salzer and Brusilovskiy [99] have published an in-depth review of the quantitative properties of the Recovery Assessment Scale, based on 77 articles that included psychometric data. They concluded that these studies indicate very good results for internal consistency, test-retest reliability, and internal reliability. Among the tools available to empirically assess recovery, this scale has been the most published. Its items cover the following five dimension scales: (1) personal confidence (9 items, Cronbach α=0.86), (2) willingness to ask for help (3 items, Cronbach α=0.83), (3) goal and success orientation (5 items, Cronbach α=0.68), (4) reliance on others (4 items, Cronbach α=0.65), and (5) no domination by symptoms (3 items, Cronbach α=0.73).

##### The Citizenship Measure

The Citizenship Measure was developed through a community-based participatory research design in response to a prompt (*For me, being a citizen means…*) suggested by persons living with MHPIs who were involved as research partners and research staff. The Citizenship Measure items cover the following five dimensions: (1) self-determination (6 items, Cronbach α=0.67), (2) respect by others (4 items, Cronbach α=0.74), (3) involvement in the community (4 items, Cronbach α=0.65), (4) basic needs (5 items, Cronbach α=0.60), and (5) access to services (4 items, Cronbach α=0.60).

When completing the Recovery Assessment Scale and Citizenship Measure questionnaires, participants will be asked to rate on a 5-point Likert scale (1=strongly disagree, 5=strongly agree) the extent to which the respective statements apply to them since the COVID-19 pandemic (in French: *situation depuis le début de la période COVID-19*). To simplify the instructions, COVID-19 will be referred to as “the virus.” Although COVID-19 actually refers to the disease and SARS-CoV-2 is the virus, in line with the developers of the COVID-19 Stress Scales, we expect that many respondents will not be aware of this distinction. Based on feedback from the pilot testing, respondents readily understood what the developers of these scales were referring to.

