## Discussion

Qualitative and quantitative results will be provided to all stakeholders and knowledge users, and posted on our massive open online course (MOOC) platform. Several PSWs and engaged service users take turns as teaching partners in *The Fundamentals of Recovery* MOOC [112], for which there are 1553 registrants from 51 different countries (Multimedia Appendix 1).

MOOCs are free interactive step-by-step courses developed by universities with the aim of reaching an unlimited number of participants and to create a community of lifelong e-learners (electronic learners). PSWs will be involved in the presentation and discussion of the findings, and acknowledged as coauthors in the publications, whenever appropriate, including within the MOOC (second edition). Indeed, the MOOC will be used as a knowledge translation platform for ongoing discussion among registrants, and updated with the findings of this pilot study in particular. Undoubtedly, the COVID-19 pandemic has disrupted many aspects of academic medical missions [113]. When the pandemic has subsided, although there will likely be some “return to normal,” some of the innovations developed in response to the COVID-19 pandemic will most likely remain a part of academic psychiatry’s everyday clinical and educational operations. The MOOC was not originally conceived as an innovative response to any particular pandemic. It has been nevertheless particularly appreciated in times of lockdown due to the COVID-19 pandemic. For the first 20 weeks of 2020, Figure 1 shows the cumulative total of registrants, whereas Figure 2 shows the weekly variations of new registrants to the MOOC; both figures show accelerated counts since WHO officials announced on March 11, 2020, that the COVID-19 contagion should henceforth be considered a pandemic.

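### Both primary-outcome questionnaires ask about the whole time since the start of the COVID-19 period at T1 and again at T2, so most of the follow-up window precedes the workshops and the measured effect is pulled towards zero by an unknown amount

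*Protocol article*

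**What the plan says.** The protocol article makes personal-civic recovery the primary outcome (Primary and Secondary Outcome Measures). It is measured by the Recovery Assessment Scale (9+3+5+4+3 = 24 items) and the Citizenship Measure (6+4+4+5+4 = 23 items), 47 items together.

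One instruction covers both, given under The Citizenship Measure: "When completing the Recovery Assessment Scale and Citizenship Measure questionnaires, participants will be asked to rate on a 5-point Likert scale" the extent of agreement with each statement, that is, "the extent to which the respective statements apply to them since the COVID-19 pandemic". The French text is more explicit about the fixed starting point: "situation depuis le début de la période COVID-19".

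Under Outcome Measures at Follow-up, "the measures of personal-civic recovery (47 items) will be repeated". No different reference period is given for follow-up there or anywhere else.

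Table 2 places T1 in August 2020, the ten weekly groups in September to October, and T2 in November. Quantitative Analyzes plans to analyse within-patient change from baseline with a paired t test, run separately in the intervention and control groups, with confidence intervals and effect sizes then compared between them.

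**The concern.** A change score shows an intervention effect only if the follow-up rating can move away from the baseline rating. Here the follow-up window includes the baseline window. A participant who takes the instruction literally in November must give weight to spring and summer 2020, months already rated in August and which the workshops could not have altered.

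The control arm does not remove this. Both arms share the pre-intervention stretch, so the difference between arms shrinks as well as the change within each arm.

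The article wants to detect an effect specifically attributable to the peer support workers and to collect data for a later RCT (Principal Research Questions). A small or null change could reflect the wording of the questionnaire rather than the intervention. An effect size or SD of change taken from these data would be a poor basis for planning the RCT.

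**Working it through.** The article states no figure for the reference window and no power calculation, so there is nothing of its own to reproduce. The check is date arithmetic on its calendar.

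**Inputs**
- Start of the window: the instruction gives no date. The only pandemic date in the article is in the Discussion, on course registrations: "WHO officials announced on March 11, 2020, that the COVID-19 contagion should henceforth be considered a pandemic". I take 11 March 2020 as an assumed start.
- T1: August 2020; workshops from September 2020; T2: November 2020 (Table 2, months only).

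**Step 1. Share of the T2 window before the workshops**

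Share = (days from start to first workshop) / (days from start to T2). With workshops from 1 September, the numerator is 174 days.
- T2 on 1 November: 174/235 = 74%
- T2 on 15 November: 174/249 = 70%
- T2 on 30 November: 174/264 = 66%

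Moving the first workshop to 7 or 15 September and the pandemic start to 1 or 31 March widens the range to 63–81% (154/244 to 198/245). The conclusion that most of the window is pre-intervention does not depend on the exact dates.

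**Step 2. Overlap of the T1 and T2 windows**

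From 11 March to 1 August is 143 days, and to 31 August 173 days. The T1 window therefore makes up between 143/264 = 54% and 173/235 = 74% of the T2 window, and lies wholly inside it.

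**Step 3. What this could do to the effect**

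Let w be the share from step 1. Suppose a respondent weights every day of the window equally and the full effect is present from the first workshop. Then

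T2 rating = w × (level before) + (1 − w) × (level after),

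and the effect seen is (1 − w) times the true effect:
- w = 74%: 61/235 = 26% retained
- w = 70%: 75/249 = 30% retained
- w = 66%: 90/264 = 34% retained

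If the benefit builds up over the ten sessions, less is retained. If the respondent answers by present state, all of it is.

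For scale only: the article's SD for the Recovery Assessment Scale is 0.78. An assumed true effect of 0.8 SD is 0.8 × 0.78 = 0.62 points. Under even weighting it would appear as 0.26 × 0.62 = 0.16 to 0.34 × 0.62 = 0.21 points.

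**The case against.** **Nobody is told to average.** The items ask for agreement with statements about matters such as confidence, goals, respect and access to services; they do not count symptom days. Many people may simply answer as they feel on the day. This stands, and it is why the size of the dilution cannot be stated. It does not rescue the wording: an anchor that everyone ignores does nothing, and one that some follow and others ignore adds noise and shrinkage.

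**The instruction does not name 11 March.** This also stands. The date is an assumption, and the wider range in the working allows for it.

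**The pandemic frame serves a purpose.** The third research question asks how the recovery potentials are affected by COVID-19, and the recruitment pool had completed the same scales before the pandemic. The COVID-19 Stress Scales measure stress and anxiety, so they are no substitute. But a short recent window at T1 or T2 in 2020 also falls within the pandemic and would still capture recovery during it.

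**It is a feasibility study, and the error favours neither arm.** True: recruitment and retention are unaffected. The article nevertheless names recovery as its primary outcome and intends to inform an RCT.

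**A stronger reading to resist.** A reader might turn 30% retained into a sample-size multiple of 1/0.30² = 11. The documents do not support this, because it holds the SD of change fixed. Under the even-weighting model, with T1 taken as the level before, change = 0.30 × (after − before), so its true-score SD shrinks by the same factor and only measurement error does not. With e the error share of the undiluted change variance, the multiple is [e + (1 − e) × 0.09]/0.09. That is 1 at e = 0, about 6 at e = 0.5 and about 11 at e = 1. The article does not give e, so no multiple should be quoted.

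**Conclusion.** The shared cumulative window is a real weakness in how the primary outcome is measured, and it rests on the article's own wording and calendar. The T2 window contains the whole T1 window. With 11 March 2020 as the assumed start, about 66–74% of it precedes the workshops.

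To the extent that respondents follow the instruction, the direction is towards no effect, both for change within an arm and for the contrast between arms. The size is not known. It runs from no dilution (answers by present state) to about 26–34% of the effect retained (even weighting and an immediate full effect), and lower still if benefit accrues gradually.

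This does not undermine the randomisation. It limits what a small or null change can be taken to mean, and how the estimates may be used for the RCT.

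**What to change.** **Wherever the questionnaires are still to be given, including the future RCT:** use one short recent window, worded identically at every time point and in the French text too, for example *during the past 2 weeks*. This costs one instruction line and an ethics notification. The downside is less direct comparability between data collected under the old and new anchors.

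**For this cohort:** re-anchoring is probably too late, since Table 1 reports T2 completed by 24 of 30 participants (7 and 10 in the experimental groups, 7 in the control group). Instead:
- Take the between-arm difference at T2, adjusted for T1, as the main estimate, in place of separate pre-post changes. This does not undo the dilution, but it makes the comparison one between arms. The cost is a change to the analysis text.
- State as a limitation that the reference window is shared between T1 and T2 and biases the estimate towards no effect by an unknown amount.
- Do not carry the observed effect size or SD of change uncorrected into the planning of the RCT.
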